#### 2.2.4. Assessment of the satisfaction with facial appearance.

Participants will answer the Satisfaction with Facial Appearance Overall (FACE-Q) questionnaire (adapted for the Portuguese language, before treatments and after a month). FACE-Q is a tool developed to measure the impact and effectiveness of facial aesthetic procedures from the patient’s perspective. The results will be tabulated and evaluated according to the sum of the grades obtained.^[4,33,34]^

### 2.3. Statistical analyses and data analyses plan

The criteria of normality and homogeneity of variances will be verified by ANOVA, normality will be verified with the Shapiro–Wilk and Kolmogorov–Smirnov tests. The chi-square test will be used to compare groups for categorical variables. Numerical variables will be compared by repeated measures ANOVA. If there is a statistical difference between the groups, Tukey post hoc test will be used. In all tests, a significance level of 0.05 will be adopted, which will result in an analysis with a 95% confidence interval. The software that can be used is SPSS 23 (IBM, New York) and Statistica 8.0 (StatSoft, TIBCO Software Inc, CA). The complete study schedule is shown in Figure 6.

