#### 2.1.3. Sample size calculation.

The sample size was calculated based on the primary outcome. The outcome considered was the classification of the Lemperle Wrinkle Assessment Scale (WAS).^[29]^ In the study by Sylvie Boisnic,^[30]^ the authors observed that the Lemperle score decreased in both groups after 12 weeks of treatment with a reduction of 1 (±0.7) point in the experimental group and 0.34 (±0.5) point in the placebo group and a statistically significant (*P* < .0002) change from baseline between the 2 groups after 8 weeks of treatment. This study was designed to detect a difference in scores between the groups, considering the mean and standard deviation of the study by Sylvie Boisnic,^[30]^ for the analysis of variance (ANOVA) with 3 groups and repeated measures, with significance level of 5% and power of 95%, with equal allocation for the three groups, requiring 24 participants per group, 72 in total. To control a possible loss, 50% can be added to the sample, with 36 participants per group, that is, 108 in total. The sample calculation was performed using the G-Power Version 3.1.9.4 program (Universität Kiel, Germany).

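### Section 2.3 makes Tukey tests depend on an unnamed effect that reads literally as the group main effect; name baseline-adjusted ANCOVA, or at least group-by-time, as the test

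*Protocol article*

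**What the plan says.** The confirmatory rule in section 2.3 of the protocol article is two sentences: "Numerical variables will be compared by repeated measures ANOVA", followed by "If there is a statistical difference between the groups, Tukey post hoc test will be used". No group-by-time term, change score or baseline covariate is named. Each numerical outcome has two time points, one before treatment and one about a month later (sections 2.2.1 to 2.2.4).

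Section 2.1.3 states the target as "This study was designed to detect a difference in scores between the groups". It takes its inputs from a cited study that found a "reduction of 1 (±0.7) point in the experimental group and 0.34 (±0.5) point in the placebo group", and it describes the calculation as being "for the analysis of variance (ANOVA) with 3 groups and repeated measures". It does not say which effect of that model was powered.

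On assumptions, section 2.3 says: "The criteria of normality and homogeneity of variances will be verified by ANOVA". Normality is then assigned to two named tests.

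**The concern.** A repeated-measures ANOVA of three groups at two visits gives three tests: group, time, and group-by-time. A difference between groups is the usual name for the first. That test compares each arm's average of baseline and follow-up. Randomised arms have equal expected baselines, so averaging halves any treatment effect, and stable differences between women in wrinkle severity stay in the error term. The treatment question is whether the arms change differently. That is the group-by-time test or, with more precision, the comparison of follow-up adjusted for baseline.

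The main-effect test does not inflate false positives. What is at stake is power: a real effect of the assumed size may fail the gate, and then no pairwise comparison of the two regimens with sham, or with each other, is made. Because the effect is unnamed, the choice between two tests of very different power could also be left until the data are seen.

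**Working it through.** **Inputs.** From section 2.1.3: reductions of 1 (SD 0.7) and 0.34 (SD 0.5), alpha 0.05, power 95%, 24 per group, and 36 per group with the loss allowance. Assumed: both active arms reduce by 1 and sham by 0.34; the SDs are SDs of change, common across arms; and the pre-post correlation ρ, which the document does not give, is varied.

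**The plan's own figure.** Pooled change SD = √((0.7² + 0.5²)/2) = √0.37 = 0.608. Difference = 1 − 0.34 = 0.66, so d = 0.66/0.608 = 1.085. A two-sided two-sample t-test on change has 94.9% power with 23 per group and 95.7% with 24, so 24 is reproduced. Then 3 × 24 = 72, and 24 × 1.5 = 36. The three-group test on change would need 21 per group with reductions 1, 1, 0.34, or 28 with 1, 0.67, 0.34.

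**Group-by-time (the test on change).** The mean of 1, 1 and 0.34 is 0.78, and the sum of squared deviations is 0.22² + 0.22² + 0.44² = 0.2904. Noncentrality λ = 24 × 0.2904/0.37 = 18.84. The noncentral F with 2 and 69 df gives 97.5% power at every ρ.

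**Group main effect.** The SD at one visit is s = 0.608/√(2(1 − ρ)). The average of the two visits has variance s²(1 + ρ)/2, and the effect is halved to 0.33. Hence λ = 18.84 × (1 − ρ)/(1 + ρ). At ρ = 0.7 this is 18.84 × 0.3/1.7 = 3.32.

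**ANCOVA.** The residual variance is s²(1 − ρ²), which is (1 + ρ)/2 of the change variance: 0.75 at ρ = 0.5 and 0.90 at ρ = 0.8, or 25% to 10% less. Hence λ = 18.84 × 2/(1 + ρ), with 2 and 68 df.

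| ρ (assumed) | SD at one visit | Main effect, λ at 24 | Main effect, power at 24 | Main effect, power at 36 | ANCOVA, power at 24 |
|---|---|---|---|---|---|
| 0.3 | 0.51 | 10.14 | 80% | 94% | 99.8% |
| 0.5 | 0.61 | 6.28 | 58% | 78% | 99.5% |
| 0.6 | 0.68 | 4.71 | 46% | 65% | 99.3% |
| 0.7 | 0.79 | 3.32 | 34% | 49% | 98.9% |
| 0.8 | 0.96 | 2.09 | 23% | 33% | 98.5% |

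**Sensitivity.**
- Graded reductions of 1, 0.67 and 0.34, 24 per group, ρ from 0.5 to 0.8: group-by-time 92%, main effect 46% to 18%, ANCOVA 97.5% to 94%.
- If 0.608 is the SD at each visit rather than of change: main-effect power is 65% at ρ = 0.3 and 48% at ρ = 0.9.
- Whole procedure for one active arm against sham, 40,000 simulated trials at ρ = 0.7, 24 per group, reductions 1, 1, 0.34: main-effect gate then Tukey on averaged scores succeeds in 20%; group-by-time then Tukey on change succeeds in 91%.

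**The case against.** The strongest reply is that the text never says main effect. Section 2.1.3 uses between-group wording for a calculation fed with change figures. Section 2.2.1 speaks of comparing how scores evolve according to group, and the abstract compares later evaluations with pre-treatment data. An analyst could fairly take the gate to be group-by-time, which loses nothing. This stands. A reader might infer that the protocol demonstrably tests the wrong effect; the document supports only that it leaves the effect unnamed, in words whose literal meaning is the unhelpful one.

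A reader might also infer that most of the planned power is lost. That depends on a correlation the document does not give. More than half of the 95% is lost only from ρ of about 0.6 upward at 24 per group, and the planned 36, if all are analysed, soften the loss.

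Nor is a mismatch with the sample size proven. Sections 2.1.3 and 2.3 name the same model and neither names the effect. The phrase "change from baseline between the 2 groups after 8 weeks of treatment" reports the cited study's result, not this trial's test. The mismatch exists only under the literal reading.

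Finally, the tested term might be left to an analysis plan, and group-by-time is itself valid. But the article does fix a model, a gate and a post hoc test, so the wording of that gate is open to correction. ANCOVA is the more precise option rather than the only acceptable one: it gains 1 to 2 points of power over group-by-time in the main setting and about 2 to 6 in the graded one.

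**Conclusion.** The point holds as a badly specified test with a better alternative at hand. Taken literally, the gate has between 80% and 23% power at 24 per group for correlations of 0.3 to 0.8, where group-by-time has 97.5% and ANCOVA at least 98.5%. Taken as group-by-time, it costs no power, and what remains is the smaller gain from baseline adjustment. The figures rest on the assumed correlation, on reading the quoted SDs as SDs of change, and on equal benefit in both active arms.

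The variance statement is a separate and smaller error. ANOVA assumes homogeneity and does not test it. No effect on any result is shown, but the SDs of 0.7 and 0.5 that the plan itself quotes make a proper check sensible.

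**What to change.** In section 2.3, make the primary analysis an ANCOVA of the follow-up WAS score with group as factor and baseline WAS as covariate. Report Tukey-adjusted pairwise differences with confidence intervals, and use the same model for OCT width and depth, the Image J measurements and FACE-Q. If repeated-measures ANOVA is kept, state that group-by-time (change from baseline) is the test and apply Tukey to change. Replace the statement that ANOVA verifies homogeneity of variances with a test that does so, such as Levene's, or use robust standard errors.

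The cost is a few sentences. Baseline is already measured for every outcome, no participants or visits are added, and both named software packages fit the model. The change should be dated before unblinded data are examined.

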**Figure 6. F6:**
[figure not shown]
Flowchart activity – study timeline. Pg 13.

## 3. Discussion

PBM, through the use of LEDs and LASERs, has shown good results in the treatment of wounds, increasing the formation of fibroblast cells, collagen synthesis, and reduction and control of inflammatory cells with a consequent increase in tissue formation.^[35]^ Recently, some studies have proposed the use of PBM for aesthetic medicine.^[36]^ The use of LED devices brings practicality and safety to applications and has also been evaluated for facial rejuvenation, mainly in the red wavelength.^[17]^ PBM is indicated for mild facial photoaging, fine wrinkles, skin damage, and texture changes. They are not indicated as replacement therapy for loss of volume, facial contour, sagging skin, or deep rhytids.^[25]^ However, dosimetric parameters, application frequencies, and total treatment time vary greatly.

In addition, the instruments used to evaluate the results are often subjective, highlighting the need for additional evaluations through more precise methodologies. This work described a randomized, controlled, double-blind clinical trial protocol based on the comparison of a treatment to be performed in 3 groups for 4 weeks: one group will receive the application of the red LED mask 3 times a week, another group will receive treatment 2 times a week and the control group will perform the simulated application of the LED mask twice a week. To increase participant compliance, a neutral face cream formulation was donated to be used by all patients at night during treatment.

The sample should be as homogeneous as possible to minimize individual biases, hence the importance of delimiting the age of participants between 45 and 60 years old, Glogau from 2 to 4, and who are in menopause. It is known that menopausal hypoestrogenism leads to changes in skin metabolism, such as changes in collagen fibers and reduced water content, favoring aging.^[37]^ Skin types II, III, and IV were chosen as inclusion criteria to standardize the melanin content of the participants, excluding the other phototypes I, V, and VI to reduce light absorption by melanin.^[38]^

Other important issues are that this protocol proposes a double-blind study and the randomization will be performed in blocks.

Self-assessment has become an important tool to evaluate the results of aesthetic procedures,^[38]^ facial changes resulting from aging can impact the quality of life, self-esteem, social relationships, and activities of individuals. Thus, preventive and corrective interventions are closely related not only to health but also to psychosocial well-being.^[8,9]^ In this sense, the FACE-Q questionnaire, validated for the Portuguese language, will be used to verify the level of satisfaction after treatment.

It is known that most studies that evaluate the face are based on subjective measures (patient satisfaction and photos) or using skin biopsy.^[20]^ The evaluation methods used in this research, are noninvasive, and double-blind and aim to evaluate a set of variables that can be affected or improved by PBM as a result of the frequency of application in the groups. Face photographs will be evaluated by 3 plastic surgeons using the wrinkle scale.^[29]^ These experts will be calibrated for this assessment and must achieve a rate of agreement among peers above 70%. The evaluation of the images by the Image J software, performed by a researcher not involved in this study, aims to bring quantitative data for visual analysis. The researcher will quantify in pixels the wrinkles of interest before and after treatment. The evaluation of wrinkles in plaster casts by OCT is a reliable and accurate method and there are few data in the literature that provide this type of evaluation. Therefore, in addition to contributing as an evaluation in this protocol, it could become a measurement tool in the area of aesthetics.

In summary, this clinical trial aims to contribute to clarifying the role of PBM application frequency in improving the appearance of the facial skin of menopausal women using qualitative and quantitative methodologies.
